Effects of mindfulness based stress reduction and focus group on dealing with job stress and emotional disturbance: a longitudinal study with randomized quasi experimental design

| Abstract  Mindfulness-based intervention (MBI) is a newly psychotherapy program. It has been evidenced to be beneficial for decreasing pain, sleep problems, stress reactions, and emotional disturbance. Knowledge of the benefit of MBI to job stress is little. Focus group is a good way to obtain a great amount of relevant information regarding with the discussed issues in a short time. However, the systematic evaluation of the effects of Focus group applying at workplace is limited. The aims of the study are (1) to explore the effects of MBI and Focus group on job stress and workers’ psychological problems, (2) to examine the influence of workers’ characteristic (gender, age, and occupation) on the effects of MBI and Focus group.  The study will adopt a longitudinal research design with randomized quasi- experimental trial. Four companies are chosen for the study. The workers at high risk for mental distress provided by the company will be invited to take part in the study. The participants from two of four companies will be randomly assigned to MBI (Group M) or the waiting-mindfulness-list control group (Group C-M). The participants from the other two companies will be randomly assigned to Focus group (Group F) or the waiting–focus-list control group (Group C-F). One hundred members will be recruited in each group. Longitudinal Data will be collected five times at pre-, during, post- the intervention and follow-up twice with a four-week interval between measurements.  The research questionnaire will include basic information, Chinese Health Questionnaire, Checklist Individual Strength Questionnaire, and Perceived Stress Scale, Job content Questionnaire. All the questionnaires are validated instruments. SPSS-13.0 will be used for statistical analysis. Repeated measure will be adopted to examine the effects between pre- and post- interventions on job stress and emotional disturbance. The comparisons between the intervention group (Group I) and the waiting-list control group (Group C) will be conducted using the chi-square test or Student’s t-test. The general linear model will incorporate repeated measures: a two-way mixed design ANOVA will be performed to determine the interactive effects and then the simple main effects of intervention and the five continuous time points for the measured dependent variables. In addition, in order to explore the influences of personal characteristics on the outcomes of the intervention with time, the interaction and simple main effects of time by gender, age, education, and occupation on the measured dependent variables will be analyzed as well.  Keywords: workplace health program; mental health; job stress |

**Introduction**

A certain level of the world’s working population has mental health-related problems. About 19% of workers in Canada had reported more than one episode of psychological distress (Marchand, Demers & Durand, 2005). In Taiwan, a cross-sectional study showed that an estimated 17% of workers suffered from serious psychological distress (Huang et al.). Action in this field should therefore be launched more aggressively. Workplace health promotion program was found to be effective on enhancing workers’ mental health (Kawakami et al. 1997; Peters & Carlson 1999; Mino et al. 2006).

Mindfulness-Based Intervention (MBI) is derived from Eastern contemplative traditions. Mindfulness involves at least five characteristics: non-reactivity to inner or external experience; observing sensations, perceptions, thoughts, and feelings with non-conditional acceptance; acting with awareness; describing sensation, emotion, and thoughts with words; and non-judging of experience (Kabat-Zinn, 2005). For the past decades, the previous studies regarding MBI have found impressive reductions in psychological morbidity and pain for the clinical groups and the mitigation of stress and enhanced emotional well-being for nonclinical samples (Witek-Janusek, et al., 2008; Carlson et al., 2004; Robinson et al., 2003). MBI was seldom applied to workplace mental health promotion; its effects on mental health for workers are worth investigating.

Focus group is defined as "carefully planned series of discussions designed to obtain perceptions on a defined area of interest in a permissive, nonthreatening environment.” (Krueger & Casey, 2009) Focus groups are a way to get information about attitudes, beliefs, feelings and emotional reactions. It is also a good method to get both individual and interactive opinions (Hwu, 2008). Focus groups can be used for program development or to evaluate an existing program or intervention. It seems to be an appropriate strategy for assessing job strain among workers. However, the systematic evaluation of the effects of Focus group applying at workplace is limited.

**Purpose of the study**

The aims of the study are to determine the effectiveness of MBI and Focus group as a workplace health promotion program on psychological distress, prolonged fatigue, job strain (job control and job demand), and perceived stress and to explore the influences of personal characteristics (including gender, age, education, and occupation) on the outcomes of each intervention with time.

**Method**

Study design and the participant

The study will adopt a randomized controlled study design. Four manufacturing factories are chosen for this study. All the full-time workers in the factories will be requested to fill out a questionnaire regarding mental health and job content. The screening procedure was approved by the Institutional Review Board of the Changhua Christian Hospital. After pre-interventions assessment, the workers with psychological distress and job strain would be invited to participant in the study. The workers who are willing to take part in the study will need to give their informed consent and will be the participants for the study. The participants from two of four companies would be allocated into the MBI group (Group M) or the waiting-mindfulness-list control group (Group C-M) by block randomization. The participants from the other two companies will be randomly allocated to Focus group (Group F) or waiting-Focus-list control group (Group C-F). Each group is expected to have about 100 participants. The real number of participants in each group will be depended on how many workers are willing to take part in the study.

Study procedure

After pre-interventions assessment, the workers with psychological distress and job strain would be invited to participant in the study. All the participants will to need to give their written informed content to the research team. The researchers will assign the participants into the intervention groups or control groups by block randomization. After randomization, two well-trained research assistants will notify each participant about the group he or she will take part. The intervention groups will be led by the relevant experts. The contents of the interventions are list below. All the participants would be measured five times with an interval of four weeks between measurements. These measurements will be taken at pre-intervention (T1), at mid-intervention (T2), at the completion of intervention (T3), four weeks after intervention (T4), and eight weeks after intervention (T5). The research assistants will distribute and collect the questionnaire.

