**Checklist Individual Strength questionnaire.** The Checklist Individual Strength questionnaire (CIS), which confirmed discriminant validity and convergent validity, will be used to measure prolonged fatigue (Beurskens et al., 2000). The CIS was developed to assess the extent of the subjective fatigue, reduction in motivation, reduction in activity, and reduction in concentration. The CIS consists of 20 items on a 7-point Likert scale ranging from 1 to 7. A higher score represented a higher level of prolonged fatigue.

**Job Content Questionnaire.** The Job Content Questionnaire (JCQ) (Karasek, 1985) is a commonly used questionnaire to assess job control (including 6 items pertaining to skill discretion and 3 items pertaining to decision authority), job demands (5 items), and workplace social support (8 items). The translated Chinese version of the JCQ was reported to have acceptable psychometric properties and will be adopted in the study. For the purpose of the study, only the subscales of job control and job demands will be obtained. A higher-sum score represents a higher level of job control or job demands.

**Perceived stress.** The 10-item Perceived Stress Scale (PSS-10) developed by Cohen and his colleagues will be adopted to measure a global level of perceived stress (Cohen, et al, 1983). Participants will be asked to respond to each question on a 5-point Likert scale ranging from 0 (never) to 4 (very often). A higher total score indicates a higher level of uncontrollable, unpredictable, and overwhelming feelings.

Statistical analysis

The percentages of personal characteristics of the participants will be presented. The comparisons between Group M and Group C-M and between Group F and Group C-F will be conducted separately using the chi-square test or Student’s t-test. The general linear model will incorporate repeated measures: a two-way mixed design ANOVA will be performed individually to determine the interactive effects and then the simple main effects of each intervention and the five continuous time points for the measured dependent variables. In addition, in order to explore the influences of personal characteristics on the outcomes of each intervention with time respectively, the interaction and simple main effects of time by gender, age, education, and occupation on the measured dependent variables will be analyzed as well.

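### Each comparison pools two companies, but the stated group-by-time ANOVA has no company term: a small, avoidable loss of precision, not a bias

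*Protocol*

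**What the plan says.** The Method section, under study design, assigns companies to comparisons in pairs. For mindfulness: "The participants from two of four companies would be allocated into the MBI group (Group M"), or to the matching waiting list. For the Focus group: "The participants from the other two companies will be randomly allocated to Focus group (Group F) or waiting-Focus-list control group (Group C-F"). Planned size: "Each group is expected to have about 100 participants".

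The study procedure describes allocation as follows: "The researchers will assign the participants into the intervention groups or control groups by block randomization". It gives no stratum and no block size, and does not say whether each company has its own list.

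The Statistical analysis section keeps the two comparisons apart: "The comparisons between Group M and Group C-M and between Group F and Group C-F will be conducted separately", by chi-square or t-test. For the longitudinal outcomes, "a two-way mixed design ANOVA will be performed individually to determine the interactive effects", followed by simple main effects; the two factors are intervention and the five measurement times. The additional factors are then listed: "the interaction and simple main effects of time by gender, age, education, and occupation on the measured dependent variables will be analyzed as well". Company appears neither there nor in the analysis described in the abstract.

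**The concern.** Company is a two-level factor built into each comparison, and several outcomes (job demands, job control, perceived stress) partly reflect the workplace. The Focus group programme itself includes redesign of work content and, where applicable, participation by management. It is plausible that two factories do not move in parallel over the 16 weeks, although the protocol does not say so.

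A constant difference in level between companies cancels in the group-by-time test. It does not cancel in comparisons at a single time point (the t-tests and the simple main effects of group), where it adds to the error. A difference between companies in change does not cancel in group by time. With no company term it is counted as residual variation, and if blocks run across companies it can also reach the estimate through a chance difference in company mix between arms. What is at stake is precision and power for the intervention effect.

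**Working it through.** **The protocol's own figure.** The only size that can be checked is the total: 4 × 100 = 400, which agrees with the sample quantity in the application form. No alpha, power, effect size or SD is given, so there is no sample-size calculation to reproduce.

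**Inputs.**
- From the protocol: about 100 per arm; two companies per comparison; individual allocation in blocks; a group-by-time model.
- Assumed: two-sided alpha 0.05; SD of change within a company = 1; share of one company q = 0.5; difference between companies in change d = 0.2, 0.5 or 0.8 SD. For simplicity the test is a two-arm comparison of one change score, not the full interaction over five time points.

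**Reference effect.** With company in the model, 80% power needs an effect of (1.960 + 0.842) × sqrt(2/100) = 0.396 SD.

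**Error variance with company left out.** v = 1 + q(1 − q)d² = 1 + 0.25d², which gives 1.01, 1.0625 and 1.16.

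**Power and type I error with company left out.**
- Blocks across companies: power = Φ(2.802/√v − 1.960).
- Blocks within company, model unadjusted: power = Φ(2.802 − 1.960√v), and type I error = 2 × [1 − Φ(1.960√v)].

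| d (SD) | v | Power, blocks across companies | Power, blocks within company | Type I error, blocks within company |
| --- | --- | --- | --- | --- |
| 0.2 | 1.01 | 79.6% | 79.7% | 4.9% |
| 0.5 | 1.0625 | 77.6% | 78.3% | 4.3% |
| 0.8 | 1.16 | 73.9% | 75.5% | 3.5% |

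A 70:30 company mix gives slightly smaller losses (at d = 0.8, power 74.9% and 76.2%).

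**Simulation check, 10,000 trials per setting.**
- Blocks within company, no company term: type I error 5.0%, 4.3%, 3.5%; power 79.1%, 77.9%, 75.1%.
- Unstratified allocation, no company term: type I error 5.2%, 4.9%, 5.1%, so no inflation; power 79.2%, 77.5%, 72.5%.
- With the company term: type I error about 5% and power 79–80% in every setting.

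**Chance imbalance in company mix.**
- Workers of both companies randomly interleaved in one unstratified list: the SD of the difference in company share between arms is sqrt(2 × 0.25/100) = 0.071, so the 95% range is ±1.96 × 0.071 = ±0.139, about 14 points. Multiplied by d, the estimate moves by up to ±0.03, ±0.07 or ±0.11 SD, with mean zero. For scale, the standard error of the treatment difference is sqrt(2/100) = 0.14 SD, a 95% range of ±0.28 SD.
- Companies allocated one after the other from one list: only the block that straddles the change of company can be unbalanced. With an assumed block of 4, that is at most 2 workers, or 2 points out of 100; at d = 0.5 the shift is 0.02 × 0.5 = 0.01 SD.

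**The case against.** The strongest reply is that nothing here threatens validity. Individuals are randomised, so any shift from company mix averages zero, and it is part of the sampling error that the unadjusted analysis already estimates. This stands. A reader might infer that a company trend biases the group-by-time estimate or inflates false positives. The documents do not support that: assignment is by participant, and the test holds its level or is conservative.

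A reader might also infer that one block list runs across both companies of a pair. The protocol does not say so. It states neither a common list nor separate ones, and such detail may sit in documents not at hand. The 14-point range therefore describes one possible procedure and is not a property of this plan.

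The sizes also rest on assumed differences between companies. At 0.2 SD the loss is under one power point; the loss of 5 to 6 points needs 0.8 SD, twice the 0.396 SD treatment effect used for reference. No power target is stated, so none is missed. These limits stand as well.

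What does not stand is that the model can be left to an analysis plan. The protocol names the model, its two factors and four further characteristics, and company is not among them.

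**Conclusion.** The point holds as a matter of efficiency. The stated analysis omits a two-level factor that structures each comparison, and including it would gain precision at essentially no cost. Under the assumptions above, the loss from 80% power is under 1 point at d = 0.2, about 2 points at d = 0.5, and 5 to 6 points only at d = 0.8 (slightly more in the unstratified simulation). If blocks are formed within company, the unadjusted test is conservative.

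There is no systematic bias and no excess of false positives. Nor is company confounded with treatment in the planned analyses: each comparison is made within its own pair of companies, and the Statistical analysis section plans no contrast of mindfulness with Focus group. Whether randomisation is stratified by company is simply not stated. Severity: minor; a free improvement.

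**What to change.** - In the Statistical analysis section, add company and company-by-time as fixed effects to each of the two repeated-measures models, and keep group-by-time as the test of the intervention. Include company in the single-time-point group comparisons too. Use a fixed effect, because two companies are too few to estimate a random one.
- In the study procedure, state whether blocks are formed within company. Where allocation has not yet been done, form them within company.

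The cost is a sentence in each place. With five time points the model spends 1 degree of freedom on company and 4 on company-by-time, negligible with about 200 workers per comparison. No extra participants are needed, and no extra data, since workers are screened and recruited by factory. Fixing the term in advance also removes any later choice about whether to adjust for company.

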| Special condition | | - Intense care - Child intense care - Genetic treatment - Prosthetics | | | - Quarantine - Intravenous injection - Controlled drug - Other：________ | | | | - Surgery - CT - Gynecological supplies | |
| Inclusion criteria | | - 18 Years to 65 Years healthy employees with psychological distress and job strain - Full-time paid workers | | | | | | | | |
| Exclusion criteria | | - Age < 18y or > 65y - Part-time workers - The workers are not willing to take part in the study | | | | | | | | |
| Expected adverse event/serious adverse event | | None | | | | | | | | |
| The management of expected adverse event/ serious adverse event | | None | | | | | | | | |
| Recruit subjects | | - Media advertisement（attach the content） - TV - Radio - Newspaper - Internet - Bill board - Poster - Flyers | | | | | ■ Oral introduction   - Other________ | | | |
| Result report or publication | | Publication in academic journals or presentation in conference. | | | | | | | | |
| 1. Is there special protection in getting the informed consent of the vulnerable groups?   □Yes, specify______  □No  ■NA | | | | | | | | | | |
| 1. Is there Data safety monitoring plan, DSMP?   Explanation: except for minimal risk trials, the protocol should have DSMP. The definition of minimal risk: it means the changes or degrees of hazards caused to the body or mind is equivalent to those caused from the daily life of health subjects, conventional medicine, and psychological examination. The hazard does not increase as participating in the human trial.  □ Yes, attach DSMP protocol  ■ No | | | | | | | | | | |

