| 1. Whether the research material that does not de-link provides for specific research abroad?   □Yes, attach the warranty that the abroad research institute assure to abide by our national regulations and research material usage scope.  ■No  (Note: research material is the human specimen, nature person information, and other related data, information of the subjects.) | | | | | | | | | | |
| 1. The related procedure of obtaining informed consent:   Apply for waiver or alteration of informed consent? □No ■Yes (Please attach waive or alter informed consent checklist.)   - 1. Who explains to the subject or the legal representative about the research and obtains the consent?   □Principal investigator (including coordinate investigator)  ■Researcher  □Other doctor/research nurse (non coordinate investigator)   - 1. The language used to obtain the informed consent:   □Chinese □Taiwanese ■Chinese+ Taiwanese □Other：   - 1. Expected language understood by the subject or the legal representative   □Chinese □Taiwanese ■Chinese+ Taiwanese □Other：   - 1. The timing of obtaining the informed consent?   □Before screening  □After screening, before randomly assign  ■After screening, after randomly assign  The place of explaining the trial content? The worksites where the participant work for ；How long does it take? About 15-20 minutes | | | | | | | | | | |
| 1. Subject risk and benefit evaluation ：    1. Experiment group：   ■ Equivalent to minimal risk. (Category 1 type risk)   - Greater than minimal risk but has direct benefit to the subjects. (Category 2 type risk) - Greater than minimal risk but has no direct benefit to the subject; however, it helps understand the condition of the subjects. (Category 3 type risk) - Greater than minimal risk but has no direct benefit to the subjects; however, the research can have valuable results. (Category 4 type risk)   1. Comparator：■Yes □No(The following are optional)   ■ Equivalent to minimal risk. (Category 1 type risk)   - Greater than minimal risk but has direct benefit to the subjects. (Category 2 type risk) - Greater than minimal risk but has no direct benefit to the subject; however, it helps understand the condition of the subjects. (Category 3 type risk) - Greater than minimal risk but has no direct benefit to the subjects; however, the research can have valuable results. (Category 4 type risk) | | | | | | | | | | |

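### The role that takes consent also allocates, with no concealment described and contradictory consent timing, so enrolment could be influenced by known or partly predictable allocations

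*Protocol*

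**What the plan says.** **Allocation.** Under Study procedure in the Method section: "The researchers will assign the participants into the intervention groups or control groups by block randomization". No block size is given. Nothing says whether workers are assigned one at a time or together, who holds the sequence, or how it is concealed.

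**Consent, Method section.** Workers are surveyed, those with distress and job strain are invited, and then "All the participants will to need to give their written informed content to the research team". Assignment comes after this, and only then is the result disclosed: "After randomization, two well-trained research assistants will notify each participant about the group he or she will take part".

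**Consent, IRB application form.** Under the item "Who explains to the subject or the legal representative about the research and obtains the consent", the box for the researcher is ticked. Under timing of consent, the ticked box is "After screening, after randomly assign". The recruitment route ticked is "Oral introduction".

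**Setting.** The form marks the trial as open with a waiting-list comparator. The measures (CHQ-12, CIS, JCQ subscales and PSS-10) are all questionnaires that workers complete themselves. About 100 workers are expected in each of four groups, and the actual number depends on how many are willing.

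**The concern.** One role explains the study in person, takes consent and allocates. Screening scores exist before the approach is made. If the person approaching a worker knows, or can partly guess, the arm that worker will enter, a keen or very distressed worker can be brought forward or put off accordingly. If consent is sought after allocation, the worker may also know the arm and may accept or decline because of it.

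Either way the arms can differ in motivation and expectation before the programme starts. With an untreated comparator and self-reported outcomes, such a difference would pass into the estimated effect. Motivation is not among the listed measures, so the planned mixed-design ANOVA could not remove it. The issue is the same for both comparisons (MBI and Focus group, each against its own waiting list).

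**Working it through.** **Reproducing the plan's figure.** 4 groups × 100 = 400, which matches the sample quantity on the IRB form. Each comparison therefore has about 200 workers, implying 1:1 allocation. No figure in the protocol fixes how predictable allocation is, so the rest is conditional.

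**Route A: the IRB form's order governs (allocate, then consent).** Every allocation exists before consent is sought. Up to all of them could be known to the person seeking consent, whatever the block size. The documents do not say whether they would be disclosed at that point, so no bias can be calculated.

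**Route B: the Method section's order governs, with one-by-one assignment.** Further assumptions are a fixed 1:1 block size m that the enroller knows, and knowledge of earlier allocations. The documents state none of these.

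- The expected share of allocations certain before they are made is 1/(m/2 + 1).
- Check for m = 4: the fourth place is always known, and the third is known when the first two match, with probability 1/3. So (1 + 1/3)/4 = 1/3.
- Enumerating every block sequence gives the same shares, together with the share guessed correctly by always naming the arm with more places left (chance is 50%):

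| Block size m | Certain in advance | Of 200 per comparison | Correct best guess |
| --- | --- | --- | --- |
| 2 | 50% | 100 | 75.0% |
| 4 | 33.3% | 67 | 70.8% |
| 6 | 25% | 50 | 68.3% |
| 10 | 16.7% | 33 | 65.3% |
| 20 | 9.1% | 18 | 61.7% |

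**Route C: the Method section's order governs, with a closed list randomised in one batch.** There is no next allocation to predict: 0% foreseeable at enrolment.

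**Illustration of bias under Route B.** Assume that steering in the foreseeable share shifts prognosis by 0.3 SD between arms. This value is an assumption with no basis in the documents. Bias = share × shift:

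- m = 2: 0.50 × 0.3 = 0.15 SD
- m = 4: 0.333 × 0.3 = 0.10 SD
- m = 6: 0.25 × 0.3 = 0.075 SD
- m = 10: 0.167 × 0.3 = 0.05 SD
- m = 20: 0.091 × 0.3 = 0.03 SD

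The bias scales directly with the assumed shift, so half the shift gives half the bias, and no steering gives none. For comparison, the standard error of a standardised difference with 100 per arm is √(2/100) = 0.14 SD.

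**The case against.** The strongest reply is that the Method section describes a cohort procedure: survey everyone, invite those who qualify, take consent, assign, then notify. Those assigned have by then consented, and the intervention table starts from a common week 0. That fits batch allocation at least as well as sequential entry, and under batch allocation nothing upcoming can be foreseen. This stands.

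It is also fair to say that the researcher box on the form is a category and that the Method section's wording is a team label. A reader might infer that the same individuals consent workers, hold the sequence and see earlier allocations. The documents show only the same role. The open box answers a question on blinding and does not by itself say that allocation is unconcealed. A reader might equally infer that many upcoming allocations can be foreseen. That needs one-by-one entry and small, fixed, known blocks, none of which is stated.

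Finally, part of the point rests on silence about concealment and block size. The rest does not: the protocol positively gives allocation to the role that takes consent, and its two statements on consent timing contradict each other. Having research assistants notify participants does not settle this, because it governs disclosure after randomisation and not who knows the allocation when consent is sought.

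**Conclusion.** The point holds as a risk that the protocol leaves open, not as a demonstrated bias. The same role obtains consent and allocates in an open, waiting-list trial with self-reported outcomes. No concealment is described in the pages available, and the consent timing on the IRB form contradicts the Method section.

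The size depends on which procedure is followed. Up to all allocations could be known at consent under the form's order. From 9% (blocks of 20) to 50% (blocks of 2) would be certain in advance under one-by-one assignment with a known fixed block. None would be foreseeable under batch assignment of a closed list. The bias figure of about 0.1 SD for blocks of 4 is an illustration only. The sponsor should make the change, because the current text allows the harmful procedures and the safe one costs very little.

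**What to change.** Reconcile the Method section with the consent-timing item on the IRB application form, and replace the allocation sentence with text to this effect:

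*In each company, written consent and the baseline measurement (T1) are completed and the list of participants is closed before allocation. A member of the existing team who does not approach or consent workers then randomises the complete coded list in one computer-generated step. Allocations are released to the research assistants only afterwards.*

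This leaves no allocation known or predictable at enrolment, whatever the block size, and settles the order of consent and allocation. If batch assignment was always intended, the sponsor only has to write it down.

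The cost is wording in the protocol and the form. No extra staff are needed, and the common week 0 suits allocation from a closed list. The small downside is that early consenters wait until their company's list closes.
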